## Abstract

**Background/Objectives**: Despite the availability of multiple pharmacological treatment options, up to one-third of patients with depressive disorders fail to achieve adequate symptom relief following first-line antidepressant therapy, representing a major unmet clinical need. Fatty acids—including short-chain (SCFAs), medium-chain (MCFAs), and long-chain polyunsaturated fatty acids (PUFAs)—are increasingly implicated in depression pathogenesis through neuroinflammation, gut–brain axis signaling, and neurotransmitter metabolism, but their potential as predictors of antidepressant response remains largely unexplored. The primary aim is to evaluate whether baseline fatty acid profiles can predict pharmacological antidepressant treatment efficacy. The secondary objective is to assess the association between blood fatty acid profile and clinical presentation of depressive disorders. **Methods**: Sixty adults diagnosed with depressive disorders (ICD-11) at the initiation of a new antidepressant treatment will be recruited from psychiatric settings. Fasting blood samples collected at baseline will undergo gas chromatographic analysis of fatty acid methyl esters (FAMEs) and GC-MS quantification of SCFAs (acetic, propionic, and butyric acids). Clinical outcomes will be assessed at baseline and at 3, 6, and 12 weeks using the Beck Depression Inventory-II (BDI-II) and the Depression Anxiety Stress Scales (DASS-42). The primary endpoint is the change in BDI-II total score from baseline to week 6. Treatment response, defined as a ≥50% reduction in BDI-II total score at week 6, and remission, defined as a BDI-II score ≤12 at week 6, will be examined as secondary outcomes. Dietary habits, physical activity, quality of life, and anthropometric parameters will be collected as potential confounders. **Discussion**: This study is among the first prospective investigations to comprehensively characterize the circulating fatty acid spectrum as potential predictors of antidepressant outcomes. Findings may support identification of metabolic phenotypes of depression and contribute to personalized treatment strategies.

## 1. Introduction

### 1.1. Background

Depressive disorders are among the most prevalent mental health conditions worldwide. However, despite the availability of multiple pharmacological treatment options, up to one-third of patients fail to achieve adequate symptom relief following first-line antidepressant therapy, leaving them with persistent symptoms and significantly impaired functioning [1,2]. It causes a tremendous burden, including unemployment, loss of productivity, and increased health care costs. This substantial burden highlights the need for accessible biomarkers that could help identify patients more or less likely to respond to antidepressant treatment [2].

Among polyunsaturated fatty acids (PUFAs), eicosapentaenoic acid (EPA), arachidonic acid (AA), and docosahexaenoic acid (DHA) are of particular interest because of their involvement in neuronal membrane function and lipid-derived signaling. Clinical and observational studies have reported lower circulating EPA concentrations, a reduced EPA, and a relative predominance of DHA in individuals with depressive disorders compared with healthy controls [3,4]. Differences have also been observed in erythrocyte fatty acid composition, including higher n-6 ratios, higher AA relative to EPA and DHA, and lower absolute DHA concentrations. Some cross-sectional and prospective studies further suggest that an elevated AA/(EPA + DHA) ratio is associated with greater depressive symptom severity and increased inflammatory activity [5,6,7].

Evidence from randomized controlled trials and meta-analyses indicates that omega-3 supplementation may produce a modest reduction in depressive symptoms, with more consistent effects reported for EPA-predominant formulations than for DHA-predominant preparations [8,9,10]. Preparations containing at least 60% EPA of the total EPA + DHA content and providing approximately 1–2 g of EPA per day have been associated with the greatest therapeutic benefit [9,10].

Greater effects have also been reported in patients with an inflammatory phenotype, suggesting that inflammatory status may modify the clinical effects of omega-3 fatty acids. These findings provide indirect support for a model in which baseline PUFA composition may be related to treatment outcomes through inflammatory and membrane-related pathways [11,12]. Nevertheless, evidence from supplementation studies does not establish that baseline PUFA concentrations predict response to conventional antidepressant medication.

Short-chain fatty acids (SCFAs), primarily acetate, propionate, and butyrate, are produced by the anaerobic fermentation of dietary fiber by the gut microbiota. After absorption into the systemic circulation, they may influence the gut–brain axis through effects on intestinal and blood–brain barrier integrity, G protein-coupled receptor signaling, immune regulation, and neurotransmitter-related pathways [13,14].

Experimental findings further suggest that SCFAs may affect microglial activation, pro-inflammatory cytokine production, and the expression of neurotrophic factors involved in synaptic plasticity [15,16]. These mechanisms remain incompletely characterized in humans but provide a plausible framework linking altered SCFA availability with depressive symptoms and potentially with treatment responsiveness.

Altered circulating and fecal SCFA profiles have been observed in individuals with major depressive disorder (MDD) compared with healthy controls, and lower concentrations of selected SCFAs have been associated with greater symptom severity [17,18]. In particular, reduced propionic acid concentrations have been reported in individuals with metabolic depression, suggesting that propionate may represent a marker of the metabolic and microbiota-related disturbances present in a subgroup of patients with depression [19]. Although these findings do not demonstrate predictive value, they identify baseline propionic acid as a biologically plausible candidate for further investigation.

Available evidence suggests that depression is also associated with alterations in circulating and membrane concentrations of medium-chain fatty acids (MCFAs). Clinical and metabolomic studies have reported reduced levels of specific MCFAs, such as capric (C10:0) and lauric acid (C12:0), in individuals with depressive symptoms compared to healthy controls. These changes may reflect disturbances in mitochondrial energy metabolism and gut–brain axis signaling [20,21]. However, evidence concerning MCFAs remains limited, and their potential relationship with antidepressant response should be regarded as exploratory.

Taken together, these findings suggest that baseline fatty acid composition may reflect several processes potentially relevant to antidepressant response, including membrane lipid balance, inflammation, gut microbiota-related signaling, and energy metabolism. EPA, DHA, and AA may be particularly relevant to membrane and inflammatory pathways, whereas SCFAs and MCFAs may reflect microbiota-related and metabolic alterations. However, it remains unclear whether baseline fatty acid profiles are associated with subsequent treatment outcomes. Given the limited and heterogeneous evidence concerning individual fatty acids, the present pilot study will examine the full measured fatty acid panel exploratorily rather than test a single prespecified fatty acid hypothesis.

### 1.2. Aims and Hypotheses

Our aims are the following:

-The primary aim of the current pilot study is to investigate the association between baseline fatty acid profiles and the magnitude of antidepressant treatment response and to generate preliminary effect size estimates to inform the design of a future adequately powered study examining the predictive utility of fatty acid biomarkers in depression.-The secondary objective is to investigate the association between the erythrocyte membrane and serum fatty acid profiles and the clinical presentation of depressive disorders, encompassing the severity of depressive symptoms, anxiety symptoms, and stress-related symptoms, as assessed by the Depression, Anxiety and Stress Scales (DASS-42) and the Beck Depression Inventory-II (BDI-II).

We assume that the profile of long-, medium-, and short-chain fatty acids in blood may be associated with the course and clinical picture of depression. The main confounding factors are hypothesized to be diet, physical activity, and somatic comorbidities, with their treatment.

### 1.3. Outcome Measures

In our study, the primary outcome measure will be the change in depressive symptom severity as measured by the BDI-II total score from baseline to the 6-week assessment, across its three dimensions: cognitive, affective, and somatic.

The effectiveness of antidepressant treatment will be measured by changes in the BDI-II scale. According to previous research, secondary outcome measures will include remission, defined as a score of ≤12, and the minimal clinically important difference, defined as a 17.5% reduction in scores [22].

Treatment response will be operationalized as a ≥50% reduction in BDI-II total score from baseline to the 6-week assessment, consistent with established conventions in antidepressant treatment research, and will also be treated as a secondary outcome measure.

The secondary outcome measures will also include depression, anxiety, and stress symptoms assessed with the DASS-42 subscale scores and quality of life assessed with the WHOQOL-BREF instrument.

## 2. Materials and Methods

### 2.1. Study Design and Population

This protocol was prepared following the Standard Protocol Items: Recommendations for Interventional Trials (SPIRIT) 2025 guidelines, adapted to the extent applicable to the observational prospective design of the present study [23].

Participants will be recruited in the Central Teaching Hospital of the Medical University of Lodz, primary healthcare clinics, and mental health clinics in the Lodz voivodeship. The study population will consist of 60 adults diagnosed with depressive disorders according to the International Classification of Diseases, 11th (ICD-11). Eligible diagnoses will include single-episode depressive disorder, recurrent depressive disorder, and dysthymic disorder, reflecting the spectrum of conditions characterized primarily by depressive symptomatology. Additionally, participants must present with a BDI-II score ≥ 15 at baseline, confirming clinically relevant depressive symptom severity at the time of enrollment.

Each participant will be at the beginning of a new pharmacological antidepressant treatment (5 days before to 5 days after treatment initiation). Antidepressant treatment will not be standardized by the study protocol, as treatment decisions will follow routine clinical practice. Antipsychotic medication used as augmentation of antidepressant treatment will not constitute an exclusion criterion but will be recorded as a combination treatment.

To qualify for the study, participants must meet all inclusion criteria and not meet any exclusion criteria listed in Table 1.

During the study, each participant will have a scheduled on-site visit, during which questionnaires will be completed, and blood samples will be collected for analysis. After centrifugation, serum aliquots and washed erythrocyte pellets will be frozen and stored under predefined biobanking conditions. Following this visit, three subsequent time points are planned—at 3, 6, and 12 weeks (follow-up)—during which the participant will receive online questionnaires to complete. Follow-up assessments will be scheduled relative to the date of antidepressant treatment initiation. At each follow-up assessment, participants will report current antidepressant treatment, dose changes, discontinuations, augmentation strategies, newly introduced concomitant medications, and psychotherapy participation. Participants will remain in the study if the antidepressant treatment is modified during follow-up. The type, date, and reason for each treatment modification will be recorded. A sensitivity analysis will be performed after excluding participants with major treatment modifications before the week 6 assessment. The time points’ schedule is also illustrated in Figure 1.

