Samples will be identified exclusively by study codes, and laboratory personnel will not have access to personal identifiers or treatment outcome data.

Blood will be collected to determine the profile of short-chain fatty acids in serum as well as the erythrocyte membrane medium- and long-chain fatty acid composition. The simultaneous assessment of erythrocyte membrane fatty acids and serum short-chain fatty acids reflects the complementary and mechanistically distinct roles these lipid fractions play in depression pathophysiology. Erythrocyte membrane fatty acid composition—particularly the balance of n-6 and n-3 polyunsaturated fatty acids—provides an integrated index of long-term fatty acid status and membrane-level inflammatory potential, reflecting dietary intake and metabolic processing over the preceding 90–120 days [38]. In contrast, serum SCFAs represent dynamic, rapidly fluctuating metabolites produced by gut microbiota fermentation, serving as proxies of gut microbial activity and gut–brain axis signaling at the time of assessment [39]. By capturing both long-term structural fatty acid status and acute microbial metabolite levels within the same participants, this study aims to provide a comprehensive and mechanistically grounded characterization of the lipid-related biological landscape associated with depressive disorders and antidepressant treatment response.

Certified reference standards of saturated, monounsaturated, and polyunsaturated fatty acids ranging from C10 to C24 will be used, including decanoic (C10:0), undecanoic (C11:0), lauric (C12:0), myristic (C14:0), myristoleic (C14:1), pentadecanoic (C15:0), palmitic (C16:0), palmitoleic (C16:1), margaric (C17:0), heptadecenoic (C17:1), stearic (C18:0), vaccenic (C18:1n7), oleic (C18:1n9), linoleic (C18:2n6), γ-linolenic (C18:3n6), α-linolenic (C18:3n3), arachidic (C20:0), eicosenoic (C20:1), eicosatrienoic (C20:3n6), arachidonic (C20:4n6), eicosapentaenoic (C20:5n3), behenic (C22:0), erucic (C22:1n9), docosatetraenoic (C22:4n6), docosapentaenoic (C22:5n3), docosahexaenoic (C22:6n3), tricosanoic (C23:0), lignoceric (C24:0), and nervonic (C24:1) acids. Heneicosanoic acid (C21:0) will be used as an internal standard.

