### 2.6. Statistical Analysis

All analyses will be exploratory and hypothesis-generating. Continuous variables will be summarized using means and standard deviations or medians and interquartile ranges, as appropriate, and categorical variables as counts and percentages. Markedly skewed fatty acid variables may be transformed. Fatty acid measures will be standardized to facilitate comparison of effect estimates. Results will be reported with 95% confidence intervals, and *p*-values will be interpreted in the context of the pilot nature of the study. The primary endpoint will be the change in BDI-II total score from baseline to week 6. Associations between individual baseline fatty acids and depressive symptom trajectories will be examined using separate linear mixed-effects models estimated with restricted maximum likelihood. Repeated BDI-II scores obtained at baseline and at weeks 3, 6, and 12 will constitute the dependent variable. Models will include time, the standardized fatty acid measure, the fatty acid-by-time interaction, age, sex, and antidepressant class as fixed effects, with a participant-specific random intercept. The prespecified primary contrast will represent the association between the baseline fatty acid measure and change in BDI-II score from baseline to week 6. Fatty acids will be analyzed individually rather than entered simultaneously into a single conventional multivariable model.

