## 3. Discussion

As highlighted earlier, the rising prevalence of depressive disorders has intensified the need for effective predictors of antidepressant treatment response. This growing clinical challenge is reflected in the increasing scientific interest in identifying reliable biomarkers of treatment efficacy, which has led to a substantial expansion of research in this area. The studies summarized in Table 2 illustrate the diversity of approaches and findings to date, underscoring both the potential and the current limitations of existing predictors of antidepressant treatment outcomes.

Compared with previous studies focusing primarily on selected inflammatory markers or individual lipid fractions, the present prospective pilot study is distinguished by its comprehensive assessment of circulating fatty acids, including short-, medium-, and long-chain fatty acids. Importantly, the inclusion of short-chain fatty acids, which are closely linked to gut microbiota metabolism, represents a novel approach in the context of antidepressant treatment response. The prospective design and 12-week follow-up allow for evaluation of fatty acids as potential predictors rather than correlates of clinical response, while the naturalistic treatment setting enhances the clinical relevance of the findings.

While the current pilot study is not powered to define definitive clinical diagnostic thresholds, it serves as a critical translational stepping stone. The primary objective is to estimate the effect sizes and variance of fatty acid parameters in relation to antidepressant response, and these estimates will allow for precise a priori sample size calculations for subsequent large-scale, multi-center cohorts designed specifically to establish predictive performance metrics, including diagnostic thresholds derived from ROC-based analyses with associated sensitivity, specificity, and positive predictive values.

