## Figures and Tables

**Figure 1 jcm-15-05081-f001:**
[figure not shown]
A schematic representation of the study timeline with delineated time points. SQ—study questionnaire, DASS-42—Depression Anxiety Stress Scales, BDI-II—Beck Depression Inventory-II, FFQ-6—Food Frequency Questionnaire-6, IPAQ—International Physical Activity Questionnaire, WHOQoL-BREF—World Health Organization Quality of Life—Brief version.

**Table 1 jcm-15-05081-t001:** Eligibility criteria.

Inclusion Criteria	Exclusion Criteria	Reasons for the Participant to Be Discontinued from the Study
1. Age ≥ 18 years	1. Pregnancy	1. Withdrawal of informed consent to participate in the study
2. Diagnosis of depressive disorder according to ICD-11 and baseline BDI-II score ≥ 15 at the time of enrollment	2. Current psychotic symptoms or a primary psychotic disorder	2. Occurrence of any of the study’s exclusion criteria
3. Beginning of a new pharmacological antidepressant treatment, defined as within ±5 days from treatment initiation	3. Depressive symptoms secondary to substance use disorders or organic disorders	
4. Ability to understand the study procedures and provide written informed consent		

**Table 2 jcm-15-05081-t002:** Selected studies investigating biological and metabolic predictors of antidepressant treatment response.

Study	Study Design	Sample Size	Type of Predictors Assessed	Follow-up Duration	Findings
Gut microbiome: A potential indicator for predicting treatment outcomes in major depressive disorder [40]	Prospective cohort study	63 patients with MDD	Gut microbiome diversity and OTUs	8 weeks	Baseline gut microbiota and lipid-related metabolites differed between responders and non-responders; a total of 20 differential metabolites between responders and non-responders that were primarily involved in lipid metabolism
Omega-3 fatty acids for inflamed depression—A match/mismatch study [11]	Randomized controlled trial	101 patients with MDD	Inflammatory status (high vs. low CRP) + EPA supplementation	12 weeks	Participants with high CRP showed greater improvement with EPA augmentation than those with low inflammation

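### The baseline visit may fall up to 5 days after the new treatment starts and no stated analysis uses that offset, which matters mainly for the three serum SCFAs

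*Protocol article*

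**What the plan says.** Four statements in the protocol article combine.

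- **Entry window.** Section 2.1 sets it at "5 days before to 5 days after treatment initiation". Table 1 repeats it: "Beginning of a new pharmacological antidepressant treatment, defined as within ±5 days from treatment initiation".
- **One baseline visit.** In section 2.1, "each participant will have a scheduled on-site visit, during which questionnaires will be completed, and blood samples will be collected for analysis". Table 1 requires "baseline BDI-II score ≥ 15 at the time of enrollment", which ties the baseline score to entry.
- **Anchor of follow-up.** "Follow-up assessments will be scheduled relative to the date of antidepressant treatment initiation" (section 2.1), so weeks 3, 6 and 12 are not counted from the baseline visit.
- **Endpoint and model.** "The primary endpoint will be the change in BDI-II total score from baseline to week 6" (section 2.6). The mixed model has time, the fatty acid, their interaction, age, sex, antidepressant class and a random intercept. The possible sensitivity covariates include adherence, hospitalization status and treatment modifications, but not the day of sampling relative to treatment start.

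On interpretation, the Discussion says that the prospective design and 12-week follow-up "allow for evaluation of fatty acids as potential predictors rather than correlates of clinical response". On the analytes, section 2.4 says that "serum SCFAs represent dynamic, rapidly fluctuating metabolites produced by gut microbiota fermentation", whereas erythrocyte composition is described as reflecting the preceding 90–120 days.

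**The concern.** To call a marker a predictor rather than a correlate of response, it should be measured before the treatment whose effect it is meant to predict. Here one pooled baseline can mix samples drawn before the first dose with samples drawn after several doses, and no stated analysis separates them.

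Two things are at stake. First, a labile analyte may reflect the first days of treatment or of a hospital stay as well as the patient's prior state. Section 2.3 expects most participants to be inpatients at baseline. If sampling day tracks time in hospital (plausible, not stated), the offset could be related to both SCFA level and measured improvement.

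Second, the baseline BDI-II feeds the primary change score, the 50% response and the 17.5% improvement outcome, and a post-dose score may already contain some change. The study's purpose is to supply effect sizes and variances for a larger study, so any mixture is carried into that design.

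**Working it through.** The protocol gives no baseline-to-week-6 interval in days, so there is no stated figure to reproduce.

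**Inputs from the article:** entry window −5 to +5 days (section 2.1, Table 1); week 6 = day 42 from initiation (section 2.1); 14-day BDI-II recall (section 2.3); erythrocyte integration 90–120 days and 29 listed erythrocyte fatty acids (section 2.4); 3 serum SCFAs; N = 60 (section 2.2).

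**Assumptions, not in the article:** the baseline visit falls inside the entry window; week 6 is completed exactly on day 42; BDI-II falls on average 11 points over 6 weeks at a constant rate; the SD of the change score is 10; entry is uniform over the window.

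**1. Interval.** Interval = 42 − baseline day.
- Baseline on day +5: 42 − 5 = 37 days.
- Baseline on day −5: 42 + 5 = 47 days.
- Spread: 10 days, and 10/42 = 23.8%.
- By the same arithmetic, week 3 is 16 to 26 days and week 12 is 79 to 89 days.

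Any tolerance on the questionnaire date would widen these ranges.

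**2. Share sampled after the start.** Not given; it could be anything from 0 to 100%. With uniform entry over the 11 days, days +1 to +5 hold 5/11 = 45%, or 60 × 5/11 ≈ 27 participants.

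**3. Drift in baseline BDI-II at day +5.**
- Rate: 11/42 = 0.26 points per day.
- If the score reflects the current day only: 5 × 0.26 = 1.3 points.
- If respondents average over the 14 recall days, 9 precede treatment. The cumulative fall over the other 5 is 0.26 × 5²/2 = 0.26 × 12.5, so the shift is 0.26 × 12.5/14 = 0.23 points.
- Range: 0.23 to 1.3 points.

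**4. Noise added to the change score.** To be generous to the concern, apply the same rate across the whole window.
- SD of a uniform offset: 10/√12 = 2.89 days.
- In points: 2.89 × 0.26 = 0.76.
- Share of variance: 0.76²/10² = 0.6%.

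**5. Exposure by type of predictor.**
- Erythrocyte fatty acids (29): 5/120 = 4.2% to 5/90 = 5.6% of the integration period.
- Serum SCFAs (3): the article describes them as reflecting activity at the time of assessment, so there is no comparable buffering.

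**6. Cost of adjusting.** A main effect plus offset-by-time uses 1 + 1 = 2 df if time is linear, or 1 + 3 = 4 df if the four visits are categorical.

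**The case against.** The case against giving this much weight is substantial.

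- **Size.** A reader might multiply 0.26 points per day by the full 10-day window and conclude that measured change shifts by 2.6 points. The documents do not support that: it applies an on-treatment decline to the 5 days before the first dose. Anchoring follow-up to initiation also keeps nominal time from treatment start at week 6 fixed at 42 days. This objection stands; the post-dose ceiling is about 1.3 points.
- **Scope.** A reader might infer that all the fatty acid predictors are drug-exposed. Most of the panel is erythrocyte-based, and 5 days is a small part of its integration period. Nor does the article say that antidepressants alter SCFAs within 5 days. This also stands; for SCFAs the exposure is a possibility, not a shown effect.
- **Wording.** The plan never calls the baseline pre-treatment. Its aim is association, its analyses are exploratory, and the Discussion says potential predictors. That softens the point, but the contrast with correlates is still drawn.
- **Partial cover.** Hospitalization status and adherence are already possible sensitivity covariates, and the article does not say whether time is nominal or actual days. The correct statement is therefore that no stated analysis uses the offset. Adjusting for hospitalization status would not separate pre-dose from post-dose samples.

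**Conclusion.** The concern holds in limited form. As written, the plan would pool samples and BDI-II scores from before and after the first dose under one baseline, over an interval of 37 to 47 days, while the Discussion distinguishes predictors from correlates.

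- **Serum SCFAs:** the main issue. Its size cannot be computed, because neither the share sampled after the first dose nor any early treatment effect on SCFAs is given.
- **Baseline BDI-II:** small, 0.23 to 1.3 points at day +5, given the assumed 11-point linear fall. Added variance is under 1% at an assumed change SD of 10. Bias in a fatty acid contrast would further require the offset to be related to the fatty acid level.
- **Erythrocyte fatty acids:** minor.

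The 37-to-47-day range rests on the inference that the single on-site visit lies within the entry window. The anchoring of follow-up to initiation is sensible and is not at issue.

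**What to change.** No change to visits, treatment or sample size is needed.

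1. Derive days from the first dose of the new treatment to the baseline visit. The initiation date is already needed to schedule follow-up. State how samples taken on the day of the first dose are classified.
2. Report how many participants were sampled before and after the first dose.
3. Add the offset, as a main effect plus offset-by-time, to the sensitivity covariates in section 2.6.
4. Prespecify a sensitivity analysis of the SCFA models restricted to samples taken before the first dose of the new treatment.
5. In the Discussion, confine the predictors-rather-than-correlates wording for SCFAs to results that hold in that subset.

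**Cost.** The covariate takes 2 df with linear time or 4 df with categorical visits, which is tolerable in a sensitivity model at N = 60. The restricted analysis has fewer participants and wider intervals; under uniform entry, about 27 of 60 would be lost from days +1 to +5 alone. The subset should not be described as drug-free, because the eligibility criteria require no washout of earlier treatment.
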